**Figure 1. f1:**
[figure not shown]
Flow chart of participant recruitment and completion of study activities.

### Study population

Current patients at our ambulatory practice who are 18 years and older, and are of any gender and race, are eligible for enrollment in the study. Patients who have food allergies, are pregnant or planning to become pregnant, have no access to internet, or require English language interpretation will be excluded from participation. Additional exclusion criteria are participation in nutrition counseling with our partnering organization within the past six months, current participation in a structured weight loss program, or current use of weight loss medications. Medications prescribed for other conditions but that may have a weight loss effect, for example, metformin or GLP-1 agonists prescribed for diabetes treatment or topiramate prescribed for migraine headaches, will not result in the exclusion of potential participants.

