## Data collection

### Demographic and clinical data

Participants’ date of birth, sex, race, and ethnicity will be collected as part of demographic data. Objective health data that will be collected are weight, height, hbA1c, blood pressure, prediabetes/diabetes diagnosis and classification, hypertension diagnosis and classification, diabetes and blood pressure medications, and comorbid chronic conditions. These data will be collected in-person at the baseline visit and at 16 weeks from baseline and via chart review of routine care at six and 12 months from enrollment in the study.

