### Data analysis

The independent variables in this study are study arm (healthy meals, produce box, and matched controls [standard of care]), nutrition counseling and education, and time (pre-intervention, 16 weeks, six months and 12 months). The primary dependent variable (outcome) is absolute weight change at 16 weeks between groups. The secondary dependent variables (outcomes) are as follows: i) absolute weight change at six months and 12 months from baseline; ii) change in hbA1c, dosage, and number of diabetes medications; iii) change in dosage and number of blood pressure medications, and; iv) change in numeric rating from baseline to 16 weeks for food insecurity, diet quality, depression as well as self-efficacy for health eating, healthy weight, and chronic disease management. A final outcome of interest is satisfaction rating for the interventions provided in the study, measured using a non-validated questionnaire developed for this study.

Descriptive statistics will be calculated for demographic data and for each dependent variable by group, nutrition counseling and education, and time. Separate repeated-measures ANOVAs will be conducted for each dependent variable with the between subjects factor group (healthy meals, produce box, and matched controls) and the within subjects factor time (pre-intervention and 16 weeks). *Post hoc* testing will be conducted as appropriate. Effect sizes will be calculated between pre-intervention and 16 weeks to capture the changes from pre- to post-intervention. Missing data will be analyzed using an intention-to-treat strategy. Statistical analysis will be performed by a biostatistician using SAS statistical software. The biostatistician will be blinded to the intervention for each group to eliminate potential bias during data analysis.

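### Use of drugs that can lower weight is neither matched on nor in the weight model, so the comparison of the food arms with the chart controls can be confounded in either direction

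*Protocol article*

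**What the plan says.** **Eligibility.** Study population excludes patients for "current participation in a structured weight loss program, or current use of weight loss medications". It then names a second class, "Medications prescribed for other conditions but that may have a weight loss effect", and gives examples: "metformin or GLP-1 agonists prescribed for diabetes treatment or topiramate prescribed for migraine headaches, will not result in the exclusion of potential participants". Nothing is said about how long such a drug must have been taken, or about starts after entry.

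**Controls.** Under Study design, 70 controls are taken from the electronic record once enrolment is complete. They are matched on BMI and on diagnoses of pre-diabetes or type 2 diabetes and/or hypertension. Medication is not a matching variable, and the drug exclusion is not stated for them.

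**Data.** Demographic and clinical data lists "diabetes and blood pressure medications, and comorbid chronic conditions" among the items collected at baseline, 16 weeks, six months and 12 months.

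**Analysis.** Data analysis states: "The primary dependent variable (outcome) is absolute weight change at 16 weeks between groups". The model is described as "Separate repeated-measures ANOVAs will be conducted for each dependent variable with the between subjects factor group (healthy meals, produce box, and matched controls" and, as second factor, "the within subjects factor time (pre-intervention and 16 weeks". Medication appears only as a secondary outcome: "change in hbA1c, dosage, and number of diabetes medications", and likewise for blood pressure drugs.

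**The concern.** The protocol itself identifies drugs that may move its primary outcome and admits people who take them. Enrolment requires obesity with pre-diabetes, type 2 diabetes or hypertension, so users of diabetes drugs are to be expected. Listing change in diabetes medication as an outcome shows that changes during follow-up are expected too.

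Both hypotheses under the primary aim include a comparison with standard of care, and that comparison has no randomisation behind it. If more food participants than controls recently started such a drug, part of the loss due to the drug is counted as a food effect. If controls start more of them, or use weight-loss drugs because no exclusion was applied to them, a real food effect is masked. As written, neither the matching nor the model separates the two.

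**Working it through.** **1. The planned effects.** Sample size determination assumes means of 92 kg (controls), 78.4 kg (meals) and 85.2 kg (produce), SD 16, alpha 0.05 and power 0.80. One-way ANOVA power from the noncentral F distribution is 0.789 at 27 per group and 0.805 at 28, so the stated 28 is reproduced. The planned effects against controls are 92 − 85.2 = 6.8 kg (produce) and 92 − 78.4 = 13.6 kg (meals).

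**2. What the model estimates.** With two time points, the group-by-time test is a comparison of mean weight change between groups. Let s be the share of a group whose use is recent enough, or starts during the 16 weeks, to affect weight change, and let d be the drug effect over that time. Then

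expected difference in change = food effect + (difference in s) × d.

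Stable long-term use adds about the same to both weights and largely cancels. Recent starts and changes do not.

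**3. Food arms against chart controls.** The documents give neither s nor d. Assumed range: a difference in s of 10 to 30 percentage points, and d of 2 to 6 kg.

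| Difference in s | d = 2 kg | d = 4 kg | d = 6 kg |
|---|---|---|---|
| 10 points | 0.2 kg | 0.4 kg | 0.6 kg |
| 20 points | 0.4 kg | 0.8 kg | 1.2 kg |
| 30 points | 0.6 kg | 1.2 kg | 1.8 kg |

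The range of 0.2 to 1.8 kg is 3% to 26% of 6.8 kg and 1.5% to 13% of 13.6 kg. The Discussion calls a 5% loss modest. At 92 kg that is 4.6 kg, of which the range is 4% to 39%.

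**4. Effect on the error rate.** Assume no food effect, an SD of weight change of 4 to 6 kg, and 70 food participants against 70 controls (normal approximation, matching ignored). The standard error is SD × √(1/70 + 1/70). The nominal two-sided 5% error becomes:

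| Shift | SD 4 kg | SD 5 kg | SD 6 kg |
|---|---|---|---|
| 0.4 kg | 9.1% | 7.6% | 6.8% |
| 0.8 kg | 21.9% | 15.7% | 12.4% |
| 1.2 kg | 42.7% | 29.5% | 21.9% |

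**5. Meals against produce.** Allocation is 1:1 with 35 per arm, so the expected difference in baseline use is zero. Its SD is √(2q(1 − q)/35), where q is the share of users: 7.2, 9.6 and 11.0 percentage points at q = 10%, 20% and 30%. This chance variation is part of the sampling error that the standard error already covers.

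The shares in this step must be those of recent starters when they are multiplied by a starter's weight loss. With 20% users, an assumed 5 kg loss and all users counted, the 95% limit is 1.96 × 0.096 × 5 ≈ 0.94 kg. If only one user in five started recently (4%), it is 1.96 × √(2 × 0.04 × 0.96/35) × 5 ≈ 0.46 kg. Only starts after baseline could differ systematically between these two arms.

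**The case against.** **The entry rule is open and deliberate.** A reader might infer that Study population contradicts itself. It does not: it excludes drugs used for weight loss and admits others by indication, which fits a population with diabetes and hypertension. This stands, and no change of eligibility is needed.

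**Randomisation protects the comparison of the food arms.** A reader might infer that baseline drug use biases meals against produce. It does not, for the reason in step 5. This stands.

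**The drugs are largely recorded.** A reader might infer that the data cannot show how much loss came with a drug. That goes too far: two of the three examples, metformin and GLP-1 agonists for diabetes, fall within the diabetes medications recorded at baseline and week 16. The gap is narrower. Drugs for other indications, such as the topiramate example, are not listed, and neither are start or change dates.

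**Matching on diabetes diagnosis helps.** It does, in part. A diagnosis fixes neither which drug a patient takes nor when it was started.

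**Covariates and sensitivity analyses may be in a plan not shown.** This is fair, and their absence alone would be no finding. But the article itself states the matching variables, the medication list and the factors of the weight model. Followed as written, these leave a confounder that the protocol names unadjusted in the non-randomised comparison.

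**Conclusion.** The point holds for the food arms against the chart controls. The weight difference there can be confounded, in either direction, by use or recent starts of drugs with a weight-loss effect. Matching reduces this only in part, and the stated model does not address it.

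Under the assumptions in step 3 the shift is 0.2 to 1.8 kg. That is small to moderate against the planned effects, but enough to inflate false positives if the true food effect is small. The range rests on assumed drug effects and assumed differences in recent use or starts, and it shrinks if most use is long-standing. Between meals and produce, adjustment for baseline use is a matter of precision; only differential starts after baseline could bias that comparison. The point deserves a change to the plan, and it does not invalidate the randomised comparison.

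**What to change.** 1. **Data analysis:** add baseline use of a drug with a weight-loss effect (none, recently started, longer-standing) as a covariate for weight, with the cut-off fixed before analysis. In the repeated-measures model it must enter with its interaction with time, or equivalently as a covariate in a model for weight change; a main effect alone leaves the change unadjusted. The diabetes-medication data already collected supply most of it.
2. **Demographic and clinical data:** extend the record to such drugs given for other indications, with start or change dates, and take the same record from the charts of the controls.
3. **Sensitivity analysis:** prespecify one analysis for starts or changes between baseline and week 16, with its rule stated in advance. These should not be a covariate, because a start may follow from the arm.

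Eligibility and clinical care do not change. The cost is one or two degrees of freedom, an added medication field and a little more chart abstraction.

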### Recruitment strategy

A flyer inviting patients to participate in the study will be available in patient rooms as well as in patient waiting areas at our ambulatory practice. Flyers will have contact information (phone number and email address) for the study coordinator. Potential study participants will be informed about the study by a nurse or provider during their routine office health visits. If interested, potential participants may choose to meet with the study coordinator after their visit or they may call or email the study coordinator at the phone number provided on the tear-off of the study flyer. During phone calls or email correspondence with the study coordinator, eligible participants will receive detailed information about the study, and they will be invited to come to the practice to complete the consent process and baseline visit.

### Sample size determination

Similar past research conducted in the US (Berkowitz, Delahanty, *et al.*, 2019) was used to estimate a baseline weight of 92 ± 16 kg for the study population. In order to estimate the effect size of weight loss potential in the intervention groups, the CDC healthy eating standard range of 1 to 2 pounds weight loss per week was used. The estimate for weight loss in the healthy meals group was 2 pounds per week over 15 weeks, and the estimate weight loss for the produce group was 1 pound per week for 15 weeks. It was assumed that there would be no weight change in the matched controls (standard of care) group. A one-way AONVA sample size calculation was performed using the following parameters: mean weight (kg) [matched controls 92, healthy meals 78.4, Produce 85.2], standard deviation 16 for all groups, 0.80 power, and 0.05 alpha. This yielded a sample size of 28 per group. We assume a 10% attrition rate, bringing the sample size to 35 per group.

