Adopting a healthy diet is a key lifestyle modification in the management of obesity and adiposity-linked chronic diseases. A modest weight loss of 5% of body weight has been shown to improve chronic conditions, with higher weight loss correlated with greater health outcomes (Jensen *et al.*, 2014; Ryan and Yockey, 2017). While various dietary strategies to promote weight loss exist, in general, reduced-calorie diets that are unrestrictive of macronutrient type (Sacks *et al.*, 2009) and that encourage increased dietary fiber consumption (Slavin, 2005; Anderson *et al.*, 2009) appear best suited to aid weight loss. In the landmark POUNDS Lost study, dietary fiber intake promoted weight loss, irrespective of macronutrient intake in overweight and obese adults consuming a calorie-restricted diet (Sacks *et al.*, 2009; Miketinas *et al.*, 2019). Thus, by providing food items comprised of adequate daily dietary fiber to our study participants, it is plausible that they can achieve modest weight loss within a period of 16 weeks. In this food as medicine study, the comparison between structured daily healthy meals and produce box versus standard of care is intended to assess the effect size of weight loss across study arms. Past research has demonstrated that pre-packaged portion-controlled meals versus self-selected diets resulted in weight loss among overweight or obese adults at eight weeks (Hannum *et al.*, 2004) and at 12 weeks (Rock *et al.*, 2016).

Our study’s exploratory outcomes will elucidate the effect of each intervention on diabetes and blood pressure control at 16 weeks, six months, and 12 months from baseline. Prior research on cardiometabolic changes associated with weight loss has typically utilized a single long-term time point, for example, 12 months or 24 months (Wing *et al.*, 2011; Dow *et al.*, 2013; Ahmad Zamri *et al.*, 2020; Iwamoto *et al.*, 2021); therefore, there is need to examine the cardiometabolic endpoints of weight loss in the short term and medium term. Finally, findings on food insecurity, diet quality, depression, self-efficacy for health eating, healthy weight, and chronic disease management, as well as participants’ adherence to, and satisfaction with, study interventions, will add to the mounting evidence on the impact of direct provision of healthy foods (Palar *et al.*, 2017; Berkowitz *et al.*, 2020; Wu *et al.*, 2022; Jd Steer *et al.*, 2023).

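### The stated 80% power is for attained weight with a between-person SD of 16 kg in three equal groups, not for the primary analysis of 16-week weight change with 35:35:70 participants

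*Protocol article*

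**What the plan says.** Under Sample size determination, an earlier US study "was used to estimate a baseline weight of 92 ± 16 kg for the study population". The expected losses come from a public-health range. For the first arm, "The estimate for weight loss in the healthy meals group was 2 pounds per week over 15 weeks"; the produce arm is given half that rate over the same period. Controls are assumed not to change. These figures enter a one-way ANOVA with "mean weight (kg) [matched controls 92, healthy meals 78.4, Produce 85.2], standard deviation 16 for all groups, 0.80 power, and 0.05 alpha", which gives 28 per group, raised to 35 for attrition.

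Under Data analysis, "The primary dependent variable (outcome) is absolute weight change at 16 weeks between groups". Study aims says the same. On the method, "Separate repeated-measures ANOVAs will be conducted for each dependent variable with the between subjects factor group", and time is the second factor, with two levels: before the intervention and 16 weeks.

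Study design plans 35 participants in each intervention arm and 70 matched controls.

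The article describes the expected loss in two ways. Sample size determination, and again Strengths and limitations, use one to two pounds a week over 15 weeks. The Discussion cites 5% of body weight as a modest loss that has been shown to bring benefit, and says of the participants that "it is plausible that they can achieve modest weight loss within a period of 16 weeks".

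**The concern.** The quantity that was powered differs from the quantity that will be tested. The calculation compares attained weights, so its noise is how much people differ from each other in weight. The primary analysis compares changes, so its noise is how much people differ in how far their own weight moves. For body weight over 16 weeks these two can differ greatly. The calculation also assumes three equal groups, whereas the controls will be twice the size of each intervention arm.

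As a result, the stated power does not tell the sponsor what the trial can detect. The first hypothesis of the primary aim sets meals against produce as well as against standard of care. A null result on that comparison can be read only if the detectable difference in weight change is known, and the article does not give it. Strengths and limitations warns that attrition threatens power. That risk cannot be judged from a power figure for a different outcome.

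**Working it through.** **Inputs from the article.** Means 92, 78.4 and 85.2 kg; SD 16 kg; alpha 0.05; three equal groups (Sample size determination). Expected losses: 30 lb = 13.6 kg, 15 lb = 6.8 kg, and 0. The pound-to-kilogram conversions are right. Planned allocation 35:35:70 (Study design).

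**Step 1: reproduce the 28.** For the overall F test, λ = n·Σ(μᵢ − μ̄)²/SD², with 2 and 3n − 3 degrees of freedom. The mean of the three means is 85.2, so Σ(μᵢ − μ̄)² = 6.8² + 6.8² + 0 = 92.48.
- n = 27: λ = 27 × 92.48/256 = 9.75, power 0.789
- n = 28: λ = 28 × 92.48/256 = 10.12, power 0.805

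The stated 28 reproduces exactly, as a one-way ANOVA on attained weight with the baseline SD.

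**Step 2: the error term of the planned test.** The article does not name the effect to be tested. Because the outcome is the change between groups, it must be the group-by-time effect. With two time points, that F test is the same as a one-way ANOVA on change scores. If the SD is 16 kg at both times, the SD of change is 16·√(2(1 − r)). Setting this equal to 16 gives 2(1 − r) = 1, so r = 0.5. The article gives neither r nor an SD of change, so r is an assumption, shown over a range.

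**Step 3: power for change at the plan's own losses (0, 13.6, 6.8 kg).**

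| r (assumed) | SD of change (kg) | Power, 28 per group | n per equal group for 80% | Power, 28:28:56 |
|---|---|---|---|---|
| 0.3 | 18.9 | 65% | 39 | 80% |
| 0.5 | 16.0 | 80% | 28 | 92% |
| 0.7 | 12.4 | 96% | 18 | 99% |
| 0.8 | 10.1 | 99.6% | 12 | >99.9% |
| 0.85 | 8.8 | >99.9% | 10 | >99.9% |
| 0.90 | 7.2 | >99.9% | 7 | >99.9% |
| 0.95 | 5.1 | >99.9% | 4 | >99.9% |

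The last column keeps the planned 1:1:2 ratio with 28 evaluable in each intervention arm.

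**Step 4: detectable meals-versus-produce difference.** With 10% attrition, 35 × 0.9 = 31.5, taken as 31 completers per arm. At 80% power and two-sided alpha 0.05 without adjustment, the difference is (2.00 + 0.84) × SD × √(2/31), and √(2/31) = 0.254.
- SD of change 5 kg: 3.6 kg
- SD of change 7 kg: 5.1 kg
- SD of change 9 kg: 6.5 kg

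These SDs are assumptions. The plan assumes a difference of 6.8 kg.

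**Step 5: the expected losses.** 13.6/92 = 14.8% and 6.8/92 = 7.4%. The 5% in the Discussion would be 0.05 × 92 = 4.6 kg. As a sensitivity case only, take 4.6 kg on meals and, by assumption, 2.3 kg on produce, with 31:31:63 (10% lost in every group, 70 × 0.9 = 63). Power is then about 57%, 75% and 97% at r = 0.85, 0.90 and 0.95.

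**The case against.** The strongest reply is that the choice is conservative. At the plan's own losses, any r above 0.5 makes 16 kg too large for change, and the larger control group adds power. This stands. A reader might infer from the mismatch that the trial is underpowered. The article does not support that: at its own losses and equal groups, 28 per group falls short of 80% only if r is below 0.5, which is hard to credit for body weight over 16 weeks.

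A reader might also take the Discussion's 5% as the trial's real expectation and call the planned losses wrong. That goes too far. The 5% is given there as a literature benchmark for benefit, with greater loss linked to greater benefit, and Strengths and limitations repeats one to two pounds a week as the expected loss. What remains is a tension between a loss described as modest and a planning loss of up to 14.8%. Nor would it be fair to pair a small loss with the 16 kg SD, or with three groups of 28, to produce a very low power. The first keeps an SD that does not belong to the outcome, and the second ignores the 70 controls.

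The conservative direction does not rescue the stated figure. It holds at the planned losses, whereas the smaller-loss case in step 5 gives power from below 80% to well above it, depending on r. Nor is this a detail left to an analysis plan: the article states a complete calculation, and it is for another quantity.

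**Conclusion.** The mismatch is established from the article's own text, and the source of the 28 is certain. The 80% describes attained weight in three equal groups. For weight change at the plan's losses and 28 per group, it would be right only at r of about 0.5. Over the assumed range, power runs from 65% (r = 0.3) to above 99.9% (r of 0.85 or more). At the high correlation likely for body weight, the error is on the safe side and gives no reason to recruit more participants. The fault is in what the stated power means, not in the number of patients. Confidence is high on the mismatch. The numerical range is conditional, because it rests on assumed values of r, equal SDs at the two visits, and the overall F test.

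**What to change.** Keep 35 per arm and 70 controls. Replace the calculation with one on 16-week weight change, using:
- an SD of change taken from a source, such as the practice's own chart weights, or shown over a stated range such as 5 to 9 kg;
- the group-by-time test and the planned 35:35:70 allocation, less attrition.

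Then restate the power for the primary analysis, together with the detectable meals-versus-produce difference. The values in step 4 show the form: about 3.6, 5.1 and 6.5 kg for SDs of change of 5, 7 and 9 kg.

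Reconcile the expected loss in Sample size determination and Strengths and limitations (6.8 to 13.6 kg, or 7.4% to 14.8% of 92 kg) with the modest loss that the Discussion calls plausible. Show a smaller loss, such as 5%, as a sensitivity case and not as the planning effect.

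The cost is one recalculation and some rewording, with no extra patients and no change to the planned analysis. The stated power may look less favourable in the smaller-loss case.

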Study activity	Baseline visit (W0)	Week 2 (W0–W2)	Week 3 – 15 (W3–W15)	Week 16 visit (W16 ± 7 days)	6 months	12 months
Informed consent process	x					
Anthropometric data (weight, height, and blood pressure)	x			x	x	x
HbA1c	x			x	x	x
Completion of study questionnaires	x			x		
Individual nutrition counseling session		x				
Nutrition education videos			x			

**Table 2. tbl2:** Expected viewership of nutrition education videos

	Video title			
	Introduction to nutrition	Nutrition and weight loss	Nutrition and diabetes	Nutrition and hypertension
All participants	x	x		
Participants with pre-/type 2 diabetes			x	
Participants with hypertension				x
Participants with pre-/type 2 diabetes AND hypertension			x	

The control group will comprise 70 participants matched to intervention group participants based on BMI, diagnosis of pre-type 2 diabetes/type 2 diabetes, and/or hypertension. Control group participants will be identified from the electronic medical record, Epic^®^, after enrollment of all intervention arm participants has been completed. A flow chart of participant recruitment and completion of study activities is shown in Figure 1. Our study protocol adheres to the SPIRIT guidelines for clinical trial protocols (Chan *et al.*, 2013) and is registered on ClinicalTrials.gov with identifier NCT05174078.

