One limitation of this study is the relatively small sample size of 70 participants who will receive interventions. Consequently, participant attrition from the study will threaten the study power. A second limitation of the study is the lack of a parallel control group. Study controls will consist of 70 matched participants identified via the electronic health record from the same patient population as the intervention arm participants. Due to funding and ethical reasons, this study is unable to utilize a true control group for comparison with the intervention groups. Our study population faces many social challenges, including food insecurity; thus, it is important to ensure that would-be controls receive compensation comparable to the healthy food items received by intervention arm participants. The small amount of the study grant limits the ability to compensate or offer equivalent healthy food items to controls after the intervention period. A third limitation of this study is the relatively short timeline (16 weeks) in which the primary outcome will be assessed. Because this study will offer interventions for only 15 weeks, and to guard against the high attrition common in studies with a lengthy period of follow-up, assessing the primary outcome soon after completion of the interventions is deemed appropriate. With the expected weight loss of one to two pounds a week over the 15-week intervention period, the timeline for the primary outcome is still clinically meaningful. Additionally, biomarkers of interest will be collected via review of the electronic medical record at six months and 12 months from baseline. While these data will allow for the assessment of study outcomes longitudinally, a significant amount of missing data will hinder such a pursuit. A final limitation of the study is the lack of blinding to treatment arm assignment among assessors collecting self-reported data. To mitigate this limitation, during the baseline visit, self-reported data will be collected prior to random allocation to intervention arms. In addition, the biostatistician analyzing the data will be blinded to the treatment arms. Despite the aforementioned limitations, we anticipate that the results of this study will add to the growing body of scholarship on the impact of direct healthy food interventions on chronic diseases.

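### The sample size calculation assumes three equal groups, but the design compares 35, 35 and 70, so its control-group size is wrong and 0.80 is a floor for the omnibus test

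*Protocol article*

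**What the plan says.** Under Sample size determination, the Protocol article describes a one-way ANOVA. The inputs are "mean weight (kg) [matched controls 92, healthy meals 78.4, Produce 85.2" and "standard deviation 16 for all groups, 0.80 power, and 0.05 alpha". Matched controls are therefore one of the three groups being sized. The result is a single figure for every group: "This yielded a sample size of 28 per group. We assume a 10% attrition rate, bringing the sample size to 35 per group".

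The food arms agree with this. Study design sets 35 patients in each arm, and Randomization allocates them 1:1.

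The control group does not agree. Study design says: "The control group will comprise 70 participants matched to intervention group participants based on BMI". Strengths and limitations repeats the number: "Study controls will consist of 70 matched participants identified via the electronic health record from the same patient population as the intervention arm participants". Data analysis enters the matched controls as one level of a three-level group factor. The comparison as designed is thus 35 meals, 35 produce and 70 controls. The article does not say why the calculation uses equal groups.

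**The concern.** A per-group figure from a three-group calculation sets the size of each group, including the controls. Read literally, the sizing paragraph calls for 35 controls, while the design takes 70. The power attached to the equal-group calculation is then not the power of the comparison that will be run.

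What is at stake is interpretation. A reader would take 0.80 as the power of the trial. That single number covers two quite different situations: an omnibus test with a comfortable margin that rests on non-randomised chart controls, and a randomised comparison of meals with produce that the extra controls barely help. The second comparison is part of the first hypothesis under the primary aim. The same sentence also contains an attrition step that does not follow from its stated rate.

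**Working it through.** **Inputs (all from Sample size determination unless noted).** Means in kg: controls 92, meals 78.4, produce 85.2. SD 16 in every group. Alpha 0.05, target power 0.80, attrition 10%. Planned sizes from Study design: 35, 35 and 70.

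**Method.** Omnibus F test, with noncentrality λ = Σ nᵢ(μᵢ − μ̄)² / 16², where μ̄ is the mean weighted by group size. Degrees of freedom are 2 and N − 3. Power comes from the noncentral F distribution.

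**Step 1: reproduce the plan's figure.** With equal groups μ̄ = 85.2, and the deviations are +6.8, −6.8 and 0.
- n = 27: power 0.789.
- n = 28: λ = 28 × (6.8² + 6.8²) / 256 = 10.11, power 0.805.

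So 28 is exactly the smallest equal group size reaching 0.80. This confirms that the calculation assumed a control group the size of one food arm.

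**Step 2: check the attrition step.**
- 28 / 0.9 = 31.1, rounded up to 32.
- The shortcut 28 × 1.1 = 30.8 gives 31.
- 28 / 0.8 = 35, so 35 corresponds to 20% attrition.
- In the other direction, 35 × 0.9 = 31.5, so about 31 per food arm remain at the stated 10%.

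**Step 3: omnibus power at the planned allocation.** Worked case, 70 controls and 31 per food arm:
- μ̄ = (70 × 92 + 31 × 78.4 + 31 × 85.2) / 132 = 87.21
- λ = [70 × 4.79² + 31 × 8.81² + 31 × 2.01²] / 256 = 16.16
- power 0.954

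| Controls / meals / produce | Situation | Power |
|---|---|---|
| 28 / 28 / 28 | the plan's calculation | 0.805 |
| 35 / 35 / 35 | the plan's per-group figure, no loss | 0.891 |
| 70 / 35 / 35 | planned sizes, no loss | 0.967 |
| 70 / 31 / 31 | 10% loss in food arms, all controls evaluable | 0.954 |
| 63 / 31 / 31 | about 10% loss in every group | 0.946 |
| 70 / 28 / 28 | 20% loss in food arms | 0.941 |
| 49 / 28 / 28 | 20% loss in food arms; 30% of controls without a weight (assumption) | 0.903 |

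For comparison, 31/31/31 gives 0.847. With 31 per food arm, moving from 31 to 70 controls therefore lifts power from 0.847 to 0.954.

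**Step 4: the randomised contrast.** Meals versus produce differ by 85.2 − 78.4 = 6.8 kg. For a two-sided two-sample t test at 0.05 with SD 16:
- 31 per arm: 6.8 / (16 × √(2/31)) = 1.67, power about 0.38.
- 35 per arm: 6.8 / (16 × √(2/35)) = 1.78, power about 0.42.

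Extra controls can help this contrast only through the error degrees of freedom. With pooled error and 28 per food arm, going from 28 to 70 controls moves power from 0.349 to 0.351.

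**The case against.** The strongest reply is that 0.80 is listed among the calculation's inputs. It is a target used to find a minimum, the minimum of 28 reproduces exactly, and taking more controls than the minimum exceeds the target without falsifying it. The figure of 35 is also right for both food arms. Seventy controls for 70 treated participants looks like one match each, although the article does not spell that out. All of this stands, and it limits the point to the control-group size and to what 0.80 describes.

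Two stronger readings are tempting, and the document supports neither.
- A reader might infer that the mismatch leaves the trial underpowered. It does not: the additional controls only add omnibus power. The low power for meals versus produce comes from sizing on the omnibus test alone, not from the control count.
- A reader might infer that the warning under Strengths and limitations, that attrition threatens power, is mistaken. It refers to the 70 participants who receive food, and for the randomised contrast it is apt. The same section openly lists the lack of a parallel control group as a limitation.

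It might also be argued that attrition should not apply to controls, because they are drawn from charts after enrolment ends. But a chart control can lack a weight near 16 weeks, so counting all 70 as evaluable is the optimistic case.

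**Conclusion.** The point holds as an internal inconsistency on the safe side. The stated size contradicts the design for the control group. The 0.80 is a floor: on the plan's own inputs the omnibus test at 35:35:70 has power of about 0.95 at 10% loss (0.954 with all 70 controls evaluable, 0.946 with 63). There is no shortfall and no reason to change enrolment. The step from 28 to 35 does not follow from 10% attrition, and this too errs towards more patients.

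These figures take the plan's means and its SD of 16 kg as given. That SD is the one quoted for baseline weight; the article gives no SD for weight change. They also describe the one-way ANOVA used for sizing, whereas Data analysis plans a repeated-measures ANOVA. They show what the plan's calculation implies at the planned allocation and do not predict the power of the final analysis.

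**What to change.** Rewrite the Sample size determination paragraph as follows.

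1. Redo the calculation for 35 meals, 35 produce and 70 matched controls, with the plan's 10% loss in the food arms (about 31 left in each).
2. State an assumption for controls who lack a 16-week chart weight. On present inputs, report omnibus power of about 0.95: 0.954 with 70 evaluable controls, 0.946 with 63.
3. Say that the gain over equal groups comes from the non-randomised controls. Beside it, give the power for the randomised meals-versus-produce contrast: about 0.38 at 31 per arm and 0.42 at 35 per arm, for 6.8 kg and SD 16. The omnibus figure alone would give too favourable a picture.
4. Reconcile the attrition step: either 28 rises to 32 at 10%, or 35 is explained as an allowance of 20% or as deliberate over-recruitment.

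The cost is one rerun and one reworded paragraph, with no added patients or procedures.
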